## Abstract

**Background:**

Patient safety is a key target in public health, health services and medicine. Communication between all parties involved in gynecology and obstetrics (clinical staff/professionals, expectant mothers/patients and their partners, close relatives or friends providing social support) should be improved to ensure patient safety, including the avoidance of preventable adverse events (pAEs). Therefore, interventions including an app will be developed in this project through a participatory approach integrating two theoretical models. The interventions will be designed to support participants in their communication with each other and to overcome difficulties in everyday hospital life. The aim is to foster effective communication in order to reduce the frequency of pAEs. If communication is improved, clinical staff should show an increase in work satisfaction and patients should show an increase in patient satisfaction.

**Methods:**

The study will take place in two maternity clinics in Germany. In line with previous studies of complex interventions, it is divided into three interdependent phases. Each phase provides its own methods and data. Phase 1: Needs assessment and a training for staff (*n* = 140) tested in a pre-experimental study with a pre/post-design. Phase 2: Assessment of communication training for patients and their social support providers (*n* = 423) in a randomized controlled study. Phase 3: Assessment of an app supporting the communication between staff, patients, and their social support providers (*n* = 423) in a case-control study. The primary outcome is improvement of communication competencies. A range of other implementation outcomes will also be assessed (i.e. pAEs, patient/treatment satisfaction, work satisfaction, safety culture, training-related outcomes).

**Discussion:**

This is the first large intervention study on communication and patient safety in gynecology and obstetrics integrating two theoretical models that have not been applied to this setting. It is expected that the interventions, including the app, will improve communication practice which is linked to a lower probability of pAEs. The app will offer an effective and inexpensive way to promote effective communication independent of users’ motivation. Insights gained from this study can inform other patient safety interventions and health policy developments.

**Trial registration:**

ClinicalTrials.gov Identifier: NCT03855735; date of registration: February 27, 2019.

## Background

Patient safety is a key target in public health, health services, and medicine [1, 2]. In addition to medical skills and knowledge, *communication* has been shown to be a major contributor to patient safety*,* both within the healthcare team and between healthcare professionals and patients [3–5]. Communication, not only between different professionals, but also between staff members and patients or relatives, is a significant part in clinical routine each day. Important information may be lost because of the use of medical terms and may result in reduced patient safety, especially when medical terms are used with patients and their partners and relatives [3–5].

Different communication errors and barriers to effective communication have been identified in parts of the clinical team. Errors, such as the omission of important information, describe the kind of suboptimal communication behaviors, whereas barriers are obstructions to engaging in effective communication behaviors and include organizational and (inter-) personal factors such as rapidly changing healthcare teams, work overload, lack of mutual respect, not feeling part of the team, lack of self-confidence, and lack of training [6]. In a review [7] it was summarized that “effective clinical communication is respectful, clear, direct, and explicit. Consistent execution of successful communication requires excellent listening skills, superb administrative support, and collective commitment to move past traditional hierarchy and professional stereotyping.”

Studies have shown that in clinical settings, poor communication may be responsible for up to 80% of all preventable adverse events (pAEs; e.g. [4]), which are events affecting patient safety that are caused by unsafe healthcare processes, rather than by the medical condition of the patient [2]. PAEs can occur in all clinical specialties, including *gynecology and obstetrics* [9, 18]. Besides communication between healthcare providers, many studies have demonstrated that *suboptimal doctor-patient communication* is related to pAEs, including medical errors [35]. Not only is it important to communicate or disclose medical errors to patients appropriately [10] but also to communicate (more) safely and effectively in general [11]. In obstetrics, clinical routine is challenging due to high workload and risks of emergency calls (e.g., due to emergency caesarean section) as well as because medical staff is always responsible for both the mother and the fetus/newborn.

A typical example of a pAE in *gynecology and obstetrics* is the confusion of maternal and infant pulse rates during childbirth, which could result in life-long damage to the fetus due to asphyxia during childbirth (damage case analyses by [12]). This pAE may be caused by the ineffective use of available resources due to poor communication between the different partners (staff, patients and their accompanying persons/ social support providers, [13]). PAEs in gynecology and obstetrics include any physical or mental injury to the pregnant woman, fetus, or newborn due to poor communication, which may lead to incorrect medical decisions causing stillbirths, perinatal, neonatal or maternal mortality, unplanned caesarean sections, neonatal morbidity, blood loss, and hemorrhage [8].

With regard to the prevalence of pAEs, an observation study conducted in obstetrics and gynecology by November et al. in Boston, USA, identified forty-one pAEs within a time frame of 12-weeks [14]. In a recent international meta-analysis by Tanaka, Eriksson and Obermair, the incidence of adverse events in gynecological hospital admissions was 10.8% [15]. Of these adverse events, 52.5% could have been prevented and 1.2% resulted in death. The authors note that “preventability can only be assessed from available documentation and can be influenced by study personnel experience, and knowledge [ …] amendments [ …] need to take place to improve healthcare delivery in gynecology” (p. 198f). Improved communication is also likely to result in better healthcare provider and patient outcomes. For instance, a recent study has discussed the importance of communication between healthcare professionals and physician well-being. Physician burnout was associated with an increased risk for unsafe care, unprofessional behaviors, and low patient satisfaction [16–18]. This is especially true when under time constraints [6, 19, 20].

Patient satisfaction is an important patient-centric outcome for a gynecological clinic and its staff. Giving birth can be a positive experience but it can also be painful. The more pain a mother experiences and the longer her convalescence lasts, the more it affects her satisfaction. Despite healthcare providers’ awareness of this relationship, there is still room for improvement in pain treatment during labor [21]. Effective communication is one key in pain management, especially under high stress and demands. Accordingly, this needs to be improved based on empirical evidence. Empirical evidence on the effectiveness of communication training is ambiguous. Several studies show that communication errors and barriers can be reduced by efficient training programs that help individuals to identify, prevent or manage such errors and barriers. For instance, one study demonstrated that a standardized team-training program for healthcare professionals in obstetric units, based on an analysis of common causes for adverse events, was found to successfully raise professionals’ confidence in dealing with complex emergency situations [12]. Perceived ownership of staff has been demonstrated to be the key moderator of the effectiveness of such trainings [22]. However, a recent systematic review concluded that “Current evidence is inadequate to inform content of training or practice“[9]. Thus, communication *between professionals and with patients* should be structured [23, 24] specifically to the specific context. The primary aim of our project, which is theoretically grounded in models of health-related communication [11] and behavioral change (HAPA) [25], is to improve communication behaviors in gynecology and obstetrics. The second aim is to reduce pAEs and increase healthcare provider and patient satisfaction.

### Communication

A multitude of models of communication in healthcare exists. Accurate, clear communication is central to all of them. For instance, communication is one of four central aspects in the TeamStepps framework of teamwork in healthcare, which has been validated in many clinical settings, including obstetrics [26–28]. The communication dimension of this framework utilizes different tools to facilitate communication between healthcare providers, particularly in critical situations like emergencies or handovers. These tools include *check-back* (or closed-loop communication) to ensure the recipient has understood the sender’s information correctly, *callout*, which is used to convey critical information to a larger group of people efficiently, *SBAR* (an acronym standing for *situation*, *background*, *assessment* and *recommendation*), which can be used when requesting help in emergency situations, and a *checklist* for handovers [29]. The importance of sufficient, accurate and clear conveyance of information is also represented in the SACCIA model by Hannawa [11]. The acronym "SACCIA" stands for five core competencies that constitute safe communication in healthcare: "Sufficiency", "Accuracy", "Clarity", "Contextualization" and "Interpersonal Adaptation". The model has been used to classify communication causes of critical incidents, and it explains how communication errors put patient safety at risks [30].

According to the SACCIA model, focusing on transporting factual information is necessary for effective communication, but not sufficient, especially in obstetrics. Communication, and interpersonal/relational dimensions in particular, have also been identified as one of four dimensions in midwifery models of care. In obstetrics, the biomedical or pathogenic approach to patient care adopted by physicians may clash with nurses’ or midwives’ salutogenetic approaches [31]. These models consider that – unlike most other reasons to visit a hospital – birth is a natural process in most cases and a joyful moment for the parents, but it can also cause uncertainty or fear. Thus, consideration of interpersonal or relational aspects of communication with the expectant mother – such as being respectful of and taking her emotions into account – is essential to transport important information to and from the mother and accompanying persons. Moreover, focusing on interpersonal communication with other team members is likely to improve team functioning [32] and thus increase team members’ motivation to engage in more technical communication.

 In addition, the *model of relational coordination (communication between healthcare providers) and relational coproduction (communication between healthcare provider and patient,* [33]*)* is defined as ‘a mutually reinforcing process of communicating and relating for the purpose of task integration’ ([34], p. 301). It combines the technical dimensions of communication (frequent, timely, accurate, and problem-solving) with interpersonal communication goals (shared goals, shared knowledge, and mutual respect [35]). The relational aspect of this model has been adapted to the communicative process of decision-making between midwives and expectant mothers as a response to the critique that informed choice or shared decision models rely too much on factual information without taking the context or conversation partner into account [36].

If the communication competencies are practiced adequately, the quality of healthcare communication is increased and, as a result, risk of pAEs is reduced. [11]. This objective can be achieved through training sessions, and digitization (telehealth, eHealth, mHealth) [37] opens new avenues, especially in times of work concentration due to efficiency increasing, skills shortage due to few experts on the labor market, and multi-tasking as a societal trend [2, 16, 17]. There are multiple advantages to digital training, such as adaptability to the user’s needs [38], just-in-time-interventions [37] and a high number of potential users who are motivated to participate due to technological interests instead of the content, making it easier to reach rather unmotivated individuals [39, 40].

### Behavioral change

While the models described above [33, 36] provide theoretical frameworks describing communication, they do not explain how effective communication behaviors can be implemented into daily practice. For instance, the inconsistency between knowledge about pain management and actual pain management described above begs the question why mothers are not treated more adequately if professionals know about the relationship between pain and patient satisfaction. The *Health Action Process Approach* (HAPA) [25] model describes how to translate the intention/motivation to adopt a new behavior into actually adopting the behavior, and specifically takes the role of motivation and awareness of a situation into account. The HAPA model has been found useful to describe, explain and successfully improve behaviors in a variety of settings, particularly in healthcare and preventive settings [38–42]. Modules for trainings and interventions can be developed and structured based on the HAPA model (Fig. 1).

**Fig. 1 Fig1:**
[figure not shown]
Components of the HAPA model and planned training modules for improving communication competences and adopting the behavior “effective communication”

The HAPA model suggests a distinction between the (a) *motivational phase* that leads to a behavioral goal intention/motivation, followed by the (b) *volitional phase* that leads to the actual health behavior [41]. Within the two phases, different patterns of social-cognitive predictors may emerge (see Fig. 1). In the initial motivation phase (a), a person develops an intention to act. In this phase, *risk perception* is seen as a distal antecedent (e.g., “I am at risk for poor communication”). Risk perception in itself is insufficient to enable a person to form an intention. Rather, it sets the stage for a contemplation process and further elaboration of thoughts about consequences and competences. Similarly, positive *outcome expectancies* (e.g., “If I communicate effectively, I will reduce my risk for adverse events and being unsatisfied”) are most relevant in the motivation phase when a person evaluates the pros and cons of certain behavioral outcomes. One needs to believe in their capability to perform a desired action, which is conceptualized as *perceived self-efficacy* (e.g., “I am capable to communicate effectively in spite of the high time pressure or difficult communication partners”). Perceived self-efficacy operates in concert with positive outcome expectancies, both of which substantially contribute to forming an intention. Both beliefs are needed for forming intentions to adopt difficult behaviors, such as effective communication. After forming an intention, the volitional phase (b) is entered.

When a person is inclined to adopt a particular health behavior, the ‘good intention’ has to be transformed into detailed (self-)instructions on how to perform the desired action by means of planning [43]. Once an action has been initiated, it has to be maintained. This is not achieved through a single act of will but involves ongoing use of self-regulatory skills and strategies. Thus, the volitional phase should be further broken down into more proximal factors, such as planning, self-efficacy, and social support. *Social support* is one factor reflecting the barriers and resources as part of the HAPA model: Support is a resource, and the lack of it can be a barrier to adopt or maintain health behaviors [42]. Instrumental, emotional, and informational social support can enable the adoption and continuation of behaviors. Social support can be addressed by means of directly integrating important network partners. For patients in gynecology and obstetrics, this network does not only include the professional at the clinic but also their social support providers such as the spouse or partner, key family members, friends, or the attending midwife who might not be employed with the hospital [9, 20]. Therefore, a *dyadic perspective* focusing on both the patient and their social support providers should be taken. For healthcare professionals, an intervention that uses a structured and applicable approach to enhance communication might help them to communicate effectively under a heavy workload. On the one hand, negative effects of impaired physician well-being on communication might be avoided; on the other hand, it is possible that communication becomes less challenging, which relieves stress. This has been shown in the context of nursing homes [44]. We therefore aim to include stress management in the HAPA model for healthcare professionals as a training-related outcome. Multiple studies explain the usefulness of the HAPA model to describe and promote behavior and behavior change (e.g., [45] including compliance [42], hand hygiene [46, 47] and vaccination [48]).

### Research questions and hypotheses

The interventions in this study will integrate the HAPA model and SACCIA-inspired communication competencies into an advanced training delivered face-to-face in groups of clinical staff, patients and their social support providers. In addition to this, a state-of-the art intervention will make use of digital options by translating the training material into an app [39, 40]. Previous research has shown that patient coaching can be an intervention to improve communication [49–51], and professionals can also significantly benefit [52, 53].

The *research questions of this project* are the following: what is the effect of a communication training delivered face-to-face and via a digital app on effective communication behaviors? To what extent can patient and healthcare provider satisfaction be improved and pAEs be reduced by improving effective communication behaviors? “Effective communication” is defined and operationalized in this project within the "SACCIA" framework [10, 17]. Beside these main outcomes, personal (e.g., perceived stress, coping) and training-related outcomes (e.g., goal intentions, action planning) will be assessed (see Table 1).

**Table 1 Tab1:** Overview of the addressed concepts and hypotheses (numbers in brackets represent the hypotheses as described in text below)

	Phase 1	Phase 2	Phase 3
Communication competences (1., 4., 7.)	↑	↑	↑
Preventable adverse events (pAEs) (3., 6., 9.)	↓	↓	↓
Healthcare provider satisfaction (2., 8.)	↑	↑	↑
Patient satisfaction (5., 8.)	–	↑	↑
Training-related outcomes^1^ (outcome expectancies, goals and intention, action planning, coping planning, behavior, self-efficacy) (10.)	↑	↑	–
Personal outcomes (stress, coping, subjective safety culture) (10.)	↑	↑	↑
Organizational outcomes (adherence to safety culture) (11.)	↑	↑	↑

*Note:*
^1^As described in the HAPA model; ↓ = Hypotheses that criteria decreases due to the training; ↑ = Hypotheses that criteria increase; − = no evaluation planned

This will be scientifically evaluated using a three-phase study, in which phases are built sequentially on each other and described in detail in the method section: Phase 1, *implementation phase* (including needs assessment, retrospective cohort study of pAEs) *and pre-experimental study* with a group and pre−/post-test testing the effect of a training for professionals; Phase 2, *quasi-experimental efficacy study* with a randomized controlled trial study design (RCT) testing the effect of a training addressing patients and their social support providers; Phase 3, implementation of the app, aimed at staff, patients, and their social support providers, which will test the effect in *a case-control study*. Efficacy indicators are outlined in Table 1.

The *hypotheses* are the following: for Phase 1, it is expected that as a result of the training (1.) the communication competences of healthcare providers will measurably improve. As a result, (2.) healthcare providers will be more satisfied (3.) and the number and severity of pAEs should be significantly reduced for short and medium term (i.e. over the period of the intervention study and beyond). In Phase 2, it is expected that patients and their social support providers in the intervention group will develop significantly (4.) higher competences in communication with staff as well as (5.) higher satisfaction after the intervention compared to patients and their social support providers in the control group. It is also expected that (6.) the number and severity of pAEs in the intervention group will be significantly reduced compared to the number and severity of pAEs in the control group. For Phase 3, we hypothesize that the intervention group using the app compared to the intervention group without the app will show (7.) higher patient and healthcare provider communication competences and (8.) satisfaction as well as (9.) a significant reduction in the number and severity of pAEs. The effects of the training on communication competences may be (10.) mediated by training-related and personal outcomes and moderated by organizational factors (11.). All interventions in all phases will improve organizational outcomes if communication competences are improved successfully. Thus, the hypotheses will be tested in this project.

There are three aspects that make this project particularly unique. At first, previous studies have not combined the *underlying theories of communication and HAPA,* and tailored the intervention to the healthcare context. Secondly, the utilization of a *digital app* is expected to increase participation and training effectiveness. Thirdly, the project addresses healthcare providers, patients and their social support providers, regarding *all* people involved in developing effective communication and public health.

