**Fig. 2 Fig2:**
[figure not shown]
Study flow with project phases and stages, study participants and outcome (Study Flowcharts for all three Phases are in the Appendix). *Note.* The phases consist of different stages (see Table 3). Stages A to C (see Table 3) will be addressed in Phase 1. Stages D and E will be addressed in Phase 1 and 3

For the study flow of enrollment and interventions for each phase, see the Appendix. All study participants are professionals, patients and social support providers in two participating gynecology and obstetrics clinics, therefore, they receive the regular treatment as patients in terms of healthcare or as staff with human resource (HR) management. Table 2 provides a summary of outcome variables across the study phases.

**Table 2 Tab2:** Overview over the outcome variables and covariates considered in the different study phases

	Phase 1		Phase 2		Phase 3	
	T1	T2	T1	T2	T1	T2
Primary outcomes						
Communication competences^1^	X	X	X	X	X	X
Preventable adverse events (pAEs)^2^	X	X	X	X	X	X
Secondary outcomes						
Healthcare provider satisfaction^3^	X	X	X	X	X	X
Patient/treatment satisfaction^3^ (patients/social support providers)			X	X	X	X
Training-related outcomes^4^	X	X	X	X	X	X
Personal outcomes^5^	X	X	X	X	X	X
Organizational outcomes						
Adherence safety culture^6^	X	X	X	X	X	X
Subjective safety culture^7^			X	X	X	X
Covariates						
Socio-demographic variables including migration status^8^	X		X		X	

*Note:* Examples for the measurements are:

^1^ Self-developed questionnaire

^2^ Operationalized via trigger events (such as unavailable staff, equipment failure, readmissions, length of stay, communication error) as defined by [54, 55]

^3^ Nurses’ job satisfaction scale [56]

^4^ HAPA questionnaire including outcome expectancies, goals and intentions/motivation, action planning and coping planning, behavior, self-efficacy, perceived stress see [25, 42, 45–48]

^5^ Emotional exhaustion, depersonalization, perceived social support [4, 57]

^6^ The Hygiene Inventory - 23 items (HI-23) [58]

^7^ Measures equivalent to the ones used in [59, 60]

^8^ Age, gender, education, professional experience, depressive symptoms, anxiety and migration [61, 62]

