Observations for the ethnographic analyses will be recorded using a standardized observation protocol [30]. The qualitative data will be analyzed in terms of inductive content analysis and will be used to develop the training. The details of this approach are described in Sluisveld et al. (2013) [63]. Focus groups and interviews will be conducted with partially standardized guidelines with at least one person from each occupational group in order to gain an impression of potential resources and barriers as comprehensive as possible (as found by previous research, e.g. [6]) for the implementation of the intervention [22]. *Immigration background* will be considered during data collection and testing as well as during app development (i.e. it will be ensured that patients and social support providers with an immigration background will also be included in the development as cultural background was found to influence communication behaviors [9, 61, 62, 64]).

This approach will lead to a comprehensive understanding of factors that facilitate and inhibit effective communication and pAE’s. Additionally, it will identify possibilities and potential benefits for the implementation of the intervention in the field, e.g., how communication competences can be integrated into clinical practice beyond the training. Possible options include daily communication logs, regular e-mails with tips on practical application etc.

The results will be used to develop the *training for professionals* (physicians, nursing staff, training assistants, psychologists, midwives), which will be implemented in Stage E of Phase 1 in this project (*pre-experimental study*; see Fig. 4 in the Appendix). The results will also be used to develop the *training for patients and their social support providers* in a *quasi-experimental efficacy study* in Phase 2 (see Fig. 5 in the Appendix). An equivalent procedure applying and testing a training program was successfully performed in a recent study [12]. However, only staff members were addressed and no communication competences or HAPA variables were targeted. In the current study, due to theoretical, ethical and methodological reasons, all individuals should get the benefit of the training. All professionals will be assigned to the intervention group and the evaluation will be done by a pre/post comparison.

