#### Procedure, sample and data collection

Patients will be recruited via doctors and midwives in the hospitals; recruitment of staff and collection of informed consent of both patients and staff will be conducted by the on-site project managers. Quality management departments will be involved to ensure adequate participant enrollment to reach the target sample size. The target criteria of the patient sample will be evaluated statistically and clinically as in Phase 1 and 2 (see Table 2). Group differences will be tested with linear and general mixed models and with *superiority trial tests* that investigate whether the intervention is helping more than the standard care in Phase 2.

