#### Statistical analyses

To test the effectiveness of the digital app, a case-control study will be performed (see Fig. 6 in Appendix). Cases are newly recruited individuals that fulfil the inclusion criteria outlined in Table 6. Comparators/controls are the participants in one of the two intervention arms of the previously conducted RCT study in Phase 2 (i.e. patients; historical control groups; No-Treatment CG _analysis_: *N* = 176; No-Treatment CG _recruited_: *N* = 212; Previously Treated/Active CG _analysis_: *N* = 176 (called IG1 in Fig. 6 in Appendix); Previously Treated/Active CG _recruited_: *N* = 212, see in section Phase 2). *N* = 176 participants need to be analyzed for the intervention group (IG2 _analysis_). Assuming a drop-out of 20%, *N* = 212 participants have to be recruited for the intervention group (IG2 _recruited_) in Phase 3 (see Fig. 6 in Appendix). The intervention will also be provided to the professionals in the clinic. Adoption and acceptance of the intervention will be evaluated in all groups by means of observational data and self-report. Target criteria are specified in Tables 1 and 2.

At the end of Phase 3, the results from all three phases will be disseminated using a white paper with recommendations for practice. Further plans to communicate trial results to participants, healthcare professionals, the public, and other relevant groups via publication, presentations and press releases will be developed using a participatory approach, with the restriction that anonymity is ensured at all times.

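### Hypotheses 7 and 8 promise a between-group app effect in healthcare providers, but Phase 3 has no provider group without the app

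*Protocol article*

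**What the plan says.** **Phase 3 hypotheses** (Research questions and hypotheses). Hypothesis 7 reads "the intervention group using the app compared to the intervention group without the app will show (7.) higher patient and healthcare provider communication competences". Hypothesis 8 extends the same contrast to satisfaction, and Table 1 keys its provider-satisfaction row to hypotheses 2 and 8.

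**Phase 3 groups** (Phase 3, Statistical analyses). Cases are newly recruited people meeting the Table 6 criteria. Controls come from the "previously conducted RCT study in Phase 2 (i.e. patients; historical control groups", with 176 to be analysed in each of the two Phase 2 arms and 176 in the new app group. The same paragraph adds: "The intervention will also be provided to the professionals in the clinic".

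**Phase 3 analysis** (Phase 3, Procedure, sample and data collection). "The target criteria of the patient sample will be evaluated statistically and clinically as in Phase 1 and 2". The group-difference and superiority tests are described straight after that sentence.

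**Staff in Phase 1** (Phase 1, Overview of research questions and methods). "All professionals will be assigned to the intervention group and the evaluation will be done by a pre/post comparison". The training is offered to all professionals at both sites.

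**Phase 2.** Hypotheses 4 and 5 concern patients and their social support providers; hypothesis 6 concerns preventable adverse events. Allocation is by site and day of admission (Phase 2, Procedure). Table 1 nevertheless shows Phase 2 up-arrows for healthcare provider satisfaction and for adherence to safety culture. The Phase 2 Statistical analyses section refers the criteria of Tables 1 and 2 to superiority tests against standard care.

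**Table 2** schedules communication competences (listed as a primary outcome) and provider satisfaction at T1 and T2 in all three phases. Footnote 3, "Nurses’ job satisfaction scale", is attached to both provider and patient/treatment satisfaction.

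**The concern.** A hypothesis of the form A compared with B needs a B. For providers in Phase 3, A is the professionals who have the app, and B would have to be professionals who completed the face-to-face training but have no app. The article describes no such people.

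Communication competence is a primary outcome, so this affects a headline claim. If the provider part is analysed anyway, the only material is staff scores before and after the app. A rise could reflect the app, the passage of time, staff turnover or a lasting effect of the Phase 1 training. Under the present wording that rise could be read as a group difference. The article's own Discussion criticises an earlier training study for relying on a pre/post analysis without a comparison group.

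Phase 2 raises a related question about staff outcomes that are sent to an arm comparison when staff have no arm.

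**Working it through.** The question is structural, so the main check is to set each hypothesis against the groups the design creates.

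**1. What hypotheses 7 and 8 require for providers.** Two provider groups: with the app and without it. The second should have had the face-to-face training, because the article contrasts two intervention groups. An untreated group is not what is asked for.

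**2. What each phase supplies.**

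| Phase | Allocation | Healthcare provider groups |
|---|---|---|
| 1 | All professionals in one group, pre/post | 1 (all offered training) |
| 2 | Admissions by site and day, training or usual care | none allocated |
| 3 | New app group against Phase 2 arms ("i.e. patients; historical control groups") | 1 (professionals also receive the intervention) |

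Provider groups without the app in Phase 3: 0. App-free provider groups that could be brought forward from the Phase 2 arms: 0, because those arms contain patients and the people accompanying them.

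**3. What the sample size covers.** Inputs (Phase 2, Procedure): d = 0.3, alpha 0.05, power 80%. Two-sided normal approximation:

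n per group = 2(1.960 + 0.842)² / 0.3² = 174.4, rounded up to 175.

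The two-sample t-test solution is 175.4, so 176 per group and 352 in total, which reproduces the plan. Phase 3 carries the 176 forward. These figures size patient and social-support-provider groups; none is given for a provider contrast.

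**4. What the staff data could support.** This is an illustration on assumptions that are not in the article: the 140 Phase 1 professionals are also the Phase 3 staff, the effect is 0.3 SD, the test is two-sided at 0.05, and the 20% drop-out stated for patients applies (140 × 0.8 = 112).

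| Comparison | n | Power (t-test) |
|---|---|---|
| Two groups, d = 0.3 | 70 + 70 | about 42% |
| Two groups after drop-out | 56 + 56 | about 35% |
| One group pre/post, standardised change 0.3 | 140 | about 94% |
| One group pre/post after drop-out | 112 | about 88% |

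The two rows of each type answer different questions, and d = 0.3 between groups is not the same quantity as a standardised within-person change of 0.3. The table shows that a pre/post staff analysis is feasible, and that dividing the present staff into two groups would give an underpowered contrast.

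**5. Phase 2.** Hypotheses 4 to 6 contain no healthcare-provider outcome. The Table 1 provider-satisfaction row cites hypotheses 2 (Phase 1) and 8 (Phase 3), so its Phase 2 arrow has no numbered hypothesis behind it. Adherence is tied to hypothesis 11 and to a general sentence that interventions in all phases should improve organisational outcomes; neither names a comparator. The Phase 2 analysis section does name one, standard care, for the criteria of both tables. Since admissions are allocated and staff are not, that test is undefined for outcomes measured on staff.

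**The case against.** **Historical controls are the stated Phase 3 design, and app-free staff scores will exist.** Table 2 measures staff in every phase, so Phase 1 and 2 scores could serve as the comparator, confounded by time just as the patient comparison is. This stands in part: a comparison is possible. But it is a before/after comparison in what is essentially one body of staff, whereas the patient comparison is between different people in defined groups. The article also does not name staff scores as the comparator; it describes the controls as patients.

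**The full protocol or the missing figure might define a provider comparator.** The full German protocol and Fig. 6 are not at hand. A fuller document could specify how staff data are analysed, but it would have to contradict the article's account of who the controls are in order to supply a group.

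**The Phase 3 group tests may be meant for patients only.** The analysis text does follow a sentence on the patient sample. If so, the provider part of hypotheses 7 and 8 has no matching analysis, and the wording still needs to change.

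**A reader might infer that the Phase 2 provider hypotheses are equally untestable.** The article does not support that. It numbers no such hypothesis, and the Table 1 arrow is defined only as an increase, which T1 and T2 data can examine without a control. What is lost is attribution to the patient training.

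**A reader might also infer that patients will be given a nurses' job scale.** The Table 2 footnotes are introduced as examples, so this is a misplaced footnote and not evidence of the instrument chosen.

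**Conclusion.** The point holds for Phase 3. The provider parts of hypotheses 7 and 8 are worded as a between-group contrast, and the number of provider groups without the app is zero. They cannot be tested as worded. Only an uncontrolled before/after comparison is available, open to confounding by time, staff turnover and the earlier training. Because communication competence is a primary outcome, this limits what the trial can conclude and should be corrected before analysis.

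For Phase 2 the finding is narrower: two Table 1 arrows for staff outcomes without a numbered Phase 2 hypothesis on healthcare providers, and a superiority test that is undefined for staff. The footnote on the satisfaction scale is minor.

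The verdict assumes that the article's description of the Phase 3 controls is complete, and that largely the same staff care for both Phase 2 arms. The second is inferred from allocation by day within each site and is not stated outright. The patient comparisons in Phases 2 and 3 are not affected by this point.

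**What to change.** 1. **Hypotheses 7 and 8:** restrict the comparison of app with no app to patients and their social support providers.
2. **Healthcare providers in Phase 3:** state a separate hypothesis of within-provider change from T1 to T2, with T1 taken before the app is introduced. Label it uncontrolled and name time, staff turnover and the Phase 1 training as possible explanations of any change.
3. **Phase 2, Statistical analyses:** exempt staff outcomes (provider satisfaction, safety-culture adherence) from the superiority test against standard care.
4. **Table 1, Phase 2 column:** mark the provider-satisfaction and adherence arrows as uncontrolled pre/post or descriptive, or remove them.
5. **Table 2:** detach footnote 3 from patient/treatment satisfaction and cite the patient instrument there.

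Items 1 to 4 change wording only and need no further participants or measurements beyond those in Table 2. Item 5 is also a wording change if the full protocol already names a patient instrument; otherwise one must be chosen. The real cost is that the trial gives up a causal claim about the app's effect on staff, which the present design could not support.
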